### Statistical power and sample size

Sample size and power were calculated using software G Power (v. 3.1). Type I error will be controlled at two-sided 5% level. Sample size calculations were initially based on our primary QOL outcome measure (SNOT-22 scores) for objective 2, given strong evidence of improvements in the literature [33]. This was then applied to objective 1. For objective 2, detecting SNOT-22 score changes pre- and post-12 months ESS requires 9 patients for 80% power. To determine changes between treatment groups over time, considering a potential 30% cross-over between ESS and CMT groups, 106 patients are needed for 80% power, as indicated by prior data [34]. Accounting for 20% potential dropouts, our recruitment target is 150 participants, with an anticipated enrollment of approximately 170 across all centers.

Regarding ESS effects on ppFEV_1_, previous mixed results complicate clear expectations to use in power calculations for objective 1. Assuming 170 participants (factoring in 20% dropout), we will have 80% power to detect a 1.6% ppFEV_1_ change for objective 1 and a 2.3% ppFEV_1_ change for objective 1 accounting for HEMT.

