**Methods and analysis:**

This multi-institutional, observational, prospective cohort study will enroll 150 adults with PwCF+CRS across nine US CF Centers who failed initial medical therapy for CRS and elected to pursue either endoscopic sinus surgery or continue medical treatment. To determine if sinus surgery outperforms continued medical therapy in different outcomes, we will assess changes in pulmonary, CF-specific QOL, CRS-specific QOL, sleep quality, depression, headache, cognition, olfaction, productivity loss, and health utility value after treatment. The influence of highly effective modulator therapy on these outcomes will also be evaluated. This study will provide crucial insights into the impact of endoscopic sinus surgery for PwCF+CRS and aid with development of future treatment pathways and guidelines.

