All participants will be recruited from otolaryngology clinics at one of nine US institutions that are also CF Centers. Recruitment will occur at The University of California, Los Angeles (UCLA; Los Angeles, CA); University of Colorado (Aurora, CO); National Jewish Health (Denver, CO) including its affiliate Saint Joseph’s Hospital (Denver, CO); the University of Utah (Salt Lake City, UT); the Oregon Health and Science University (Portland, OR); the Medical University of South Carolina (Charleston, SC); the University of North Carolina (Chapel Hill, NC); Vanderbilt University Medical Center (Nashville, TN); and Stanford University (Palo Alto, CA); with UCLA as the coordinating site. Our recruitment goal is 150 patients. Recruitment techniques include routine face-to-face encounters, routine telephone encounters, and referrals from outside medical treatment facilities. An investigator or site coordinators using documents approved by each institution’s internal review board using Good Clinical Practice guidelines [14] will obtain written informed consent for all study participants.

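### Objective 1 power is quoted only for 170 participants, while the recruitment target is 150, and the step from 106 to 150 does not follow from 20% dropout

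*Protocol article*

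**What the plan says.** The protocol article gives the study size in four places.

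- Abstract, Methods and analysis: the study "will enroll 150 adults with PwCF+CRS across nine US CF Centers".
- Study design, eligibility, and recruitment: "Our recruitment goal is 150 patients".
- Statistical power and sample size, for SNOT-22 (Objective 2): "considering a potential 30% cross-over between ESS and CMT groups, 106 patients are needed for 80% power". The next sentence reads: "Accounting for 20% potential dropouts, our recruitment target is 150 participants, with an anticipated enrollment of approximately 170 across all centers".
- The same section, for ppFEV1 (Objective 1), where the power sentence opens: "Assuming 170 participants (factoring in 20% dropout), we will have 80% power to detect a 1.6". The figure is a percentage change in ppFEV1. Where HEMT is taken into account, the detectable change given is 2.3%.

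The section also fixes the test level: "Type I error will be controlled at two-sided 5% level". It says that the SNOT-22 sizing was carried over to Objective 1, and that earlier ppFEV1 results were too inconsistent to give a clear expected effect. It gives no SD for ppFEV1 and no group split, and does not say whether the detectable change is between groups or within patients.

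**The concern.** Three things do not fit together.

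1. The target is 150, but the only power statement for the primary pulmonary outcome assumes 170. A study that recruits exactly to target would not have the power quoted for it.
2. The text presents 150 as the result of a 20% dropout allowance on 106, and that arithmetic does not work.
3. The cross-over allowance is named for SNOT-22. The ppFEV1 sentence names only dropout, although the same patients contribute to both endpoints and Table 3 schedules cross-over data at every visit.

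At stake is how an inconclusive ppFEV1 result will be read. Readers will judge it against the published detectable change, so that figure should be the one that holds at the committed size.

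**Working it through.** **Inputs, all from Statistical power and sample size.** Two-sided alpha 0.05; 80% power; detectable changes 1.6% and 2.3% at N = 170; dropout 20%; target 150; SNOT-22 requirement 106; cross-over 30%.

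**Can 1.6% be reproduced?** No. That needs an SD, a within-patient correlation and a group split, and the article gives none. I therefore take 1.6% at 170 as correct and ask only what it becomes at 150.

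**Evaluable patients.** Reading 170 as enrolled, which matches the anticipated-enrolment sentence:
- 170 × 0.80 = 136
- 150 × 0.80 = 120

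**Detectable change at 150.** With the same SD, split, model and dropout rate, the standard error is proportional to 1/√N. The factor is √(136/120) = √(170/150) = 1.065.
- 1.6 × 1.065 = 1.70
- 2.3 × 1.065 = 2.45

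The SD and the split cancel out of this ratio.

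**Power for 1.6% at 150.** At 80% power, the effect divided by its standard error is 1.960 + 0.842 = 2.802. At 150 it is 2.802 × √(150/170) = 2.632. Power = Φ(2.632 − 1.960) = Φ(0.672) = 0.749, about 75%.

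**Alternative reading.** If 170 meant evaluable patients, 150 enrolled (120 evaluable) would give a detectable change of 1.6 × √(170/120) = 1.90 and power of about 65%. I do not rely on this reading.

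**The chain to 150.**
- 106 / (1 − 0.20) = 132.5, so 133
- Loss implied by 150: 1 − 106/150 = 29.3%
- For comparison, 106 / 0.70 = 151.4, so a loss near 30% would fit, but the text says 20%
- At 150 with 20% dropout, 120 patients remain against the 106 required

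**Cross-over, conditional only.** Suppose that 1.6% contains no cross-over allowance and that patients are analysed by initial choice. Power for a true 1.6% effect with 120 evaluable is then Φ(2.632 × f − 1.960), where f is the share of the contrast that remains.

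| Assumed f | Power |
|---|---|
| 0.85 (15% net switching) | 61% |
| 0.70 (30% switching in one group only) | 45% |
| 0.40 (30% switching in both groups) | 18% |

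The article supports none of these values of f over the others. The table shows only that the answer depends heavily on how cross-over is treated.

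**The case against.** The best defence is that 170 is openly declared. The power sentence is conditional on it, the sentence before it anticipates about that enrolment, and a target and an expected enrolment are different quantities. This stands as far as it goes: 170 is not an unsupported number, and if 170 are enrolled the 80% statement may be true. It does not explain why no figure is given for the target. Nor is 170 assured. Current status reports 87 enrolled from August 2019 to October 2023, about 50 months or 1.7 a month. At that pace 150 is about 36 months further off and 170 about 48.

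A second defence is that the effect is small and that SNOT-22, not ppFEV1, drove the sample size. Both are true, and they limit the weight of the point. The 106-to-150 step even errs on the generous side, and the sponsor may simply have rounded up; but the text attributes 150 to 20% dropout.

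Three stronger readings are tempting, and the article does not support them.

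- A reader might infer that the ppFEV1 calculation ignores cross-over. The sentence is silent, and the statement that the SNOT-22 sizing was carried over to Objective 1 leaves open that the allowance came with it. How switchers are analysed may be fixed in a fuller document.
- A reader might back-solve an SD: 1.6% with 136 evaluable patients split 1:1 in a simple two-sample comparison implies about 3.3, which could look too small. The planned analysis is a mixed model over repeated visits with covariates, which can tolerate a larger SD, and a single-group reading of the change implies about 6.7. A missing SD in a condensed article is not a fault in itself.
- A reader might conclude that the study lacks its stated power outright. Without an SD, 1.6% can be neither confirmed nor refuted.

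**Conclusion.** The point holds in a limited form. The Objective 1 power statement does not apply at the recruitment target. At 150 enrolled the detectable changes are about 1.70% and 2.45%, and power for 1.6% is about 75%: a shift of 0.10 and 0.15 in detectable change and about 5 points of power. This assumes that 1.6% and 2.3% are right at 170 enrolled, and that dropout rate, SD, split and model are the same at both sizes.

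Separately, the derivation of 150 is wrong as written, with no loss of power for SNOT-22. Whether the ppFEV1 figures allow for cross-over is not stated. If they do not, and analysis is by initial choice, power falls further by an amount that the article does not determine. It would go too far to say that the study is underpowered for ppFEV1 or that cross-over was left out.

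**What to change.** In Statistical power and sample size:

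1. Give the Objective 1 detectable changes at the 150 target: about 1.7%, and 2.45% accounting for HEMT, at 80% power with 20% dropout. Keep 1.6% and 2.3% only as the scenario for an enrolment of about 170, labelled as such.
2. Apply the 30% cross-over to the ppFEV1 calculation as was done for SNOT-22, or state that the figures already include it.
3. Correct the SNOT-22 chain to 106/0.80 = 133 and present 150 as a rounded-up target, or state the loss rate that yields 150 (about 29%).

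The cost is rewording one section. No extra patients are needed. The figures at the target become slightly less favourable, and more so if the cross-over allowance proves to be missing.

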## Current status

This study started in August 2019 and as of October 2023, we have 87 enrolled participants. We are continuing to enroll at all sites.

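### The ppFEV1 power statement rests on 170 anticipated participants rather than the recruitment goal of 150, and does not say whether the 30% cross-over assumed for SNOT-22 applies to it

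*Protocol article*

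**What the plan says.** All the planning figures are in the Protocol article, section Statistical power and sample size.

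- Error rate: "Type I error will be controlled at two-sided 5% level".
- SNOT-22, between groups: "considering a potential 30% cross-over between ESS and CMT groups, 106 patients are needed for 80% power, as indicated by prior data".
- Target: "Accounting for 20% potential dropouts, our recruitment target is 150 participants, with an anticipated enrollment of approximately 170 across all centers".
- ppFEV1, Objective 1: "Assuming 170 participants (factoring in 20% dropout), we will have 80% power to detect a 1.6% ppFEV_1_ change for objective 1".
- ppFEV1 with modulator therapy: "a 2.3% ppFEV_1_ change for objective 1 accounting for HEMT".

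The section on study design, eligibility and recruitment repeats the target: "Our recruitment goal is 150 patients". The abstract also gives 150. The power section says that the SNOT-22 sizing was carried over to Objective 1, and that mixed earlier results give no clear expectation for ppFEV1. Table 3 records cross-over at baseline and at every follow-up visit. Under Current status, "as of October 2023, we have 87 enrolled participants", from a start in August 2019.

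The article gives no SD or correlation for ppFEV1, no ESS:CMT split, no direction for the cross-over, and no rule for analysing patients who cross over.

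**The concern.** Two calculations in one section, for the same patients over the same 12 months, are described with different inputs.

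1. **Sample size.** The ppFEV1 power uses 170 participants. The number the study commits to recruit is 150. Accrual does not make 170 safe to assume: 87 patients in about 50 months is 1.74 per month, so 170 would take about 98 months in all (170/1.74).
2. **Cross-over.** The SNOT-22 between-group calculation allows for it. The ppFEV1 sentence lists its allowance in parentheses and names dropout only. A patient who changes group does so for every outcome, so the reader needs to know whether the 1.6 and 2.3 points include it.

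ppFEV1 is the primary pulmonary outcome, and the article itself calls earlier pulmonary results mixed, so a null result is plausible. Readers would then judge it against a claim of 80% power for 1.6 points. If the study has less power than that, they would credit it with excluding effects that it could well have missed.

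**Working it through.** **Inputs from the article:** two-sided 5%; 80% power for 1.6 points at 170 participants with 20% dropout; recruitment goal 150; 30% cross-over (stated for SNOT-22).

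**Assumptions added here:** 1:1 split; the 1.6 points are a difference between groups; 170 and 150 are both numbers enrolled, so 170 × 0.8 = 136 and 150 × 0.8 = 120 are evaluable.

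**Step 1: the stated figure.** Without an SD, the 80% cannot be reproduced independently. It can be taken as true and solved for the SD. With a two-sample t-test and 136 evaluable, 80% power needs a standardised difference of 0.484, so SD = 1.6/0.484 = 3.31 points. The normal approximation gives 1.6/[(1.960 + 0.842) × √(4/136)] = 3.33. This SD only carries the article's own figure to other sample sizes; it is not an outside value.

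**Step 2: 150 instead of 170, nothing else changed.**
- Detectable effect at 80% power: 1.6 × √(136/120) = 1.6 × 1.065 = 1.70 points.
- Power for 1.6 points: 75% (74.8% by t-test, 74.9% by normal approximation).
- HEMT figure: 2.3 × 1.065 = 2.45 points.

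This step needs no assumption about cross-over. It also does not depend on the SD or the split, provided both stay as they were in the original calculation. Reading 170 and 150 both as evaluable numbers gives the same ratio and the same result.

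**Step 3: if the 1.6 points do not include cross-over.** Under analysis by initially elected group, net cross-over multiplies the observed difference by a factor f, and the detectable effect of surgery is the Step 2 value divided by f. If patients who cross over are excluded instead, the evaluable number falls to 136 × 0.7 = 95 or 120 × 0.7 = 84, without dilution.

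| Reading of the 30% cross-over | Power for 1.6 at 170 | Power for 1.6 at 150 | Detectable effect of surgery at 150 |
|---|---|---|---|
| Already inside the 1.6 | 80% | 75% | 1.7 |
| Net dilution 15% (f = 0.85) | 66% | 61% | 2.0 |
| Cross-over patients excluded | 65% | 59% | 2.0 |
| Net dilution 30% (f = 0.7) | 50% | 45% | 2.4 |
| 30% in each direction (f = 0.4) | 20% | 18% | 4.3 |

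With a 30% net dilution the detectable effect at 170 is 1.6/0.7 = 2.3 points. That it matches the article's 2.3 shows nothing, because the article attributes its 2.3 to accounting for HEMT.

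**Step 4: does the SNOT-22 figure of 106 show which reading was used?** No. It can be reached in at least three ways: 52/0.7² = 106.1 (26 per group at d = 0.8, power 80.7%, effect diluted to 0.7); 74/0.7 = 105.7, rounded up (37 per group at d of about 0.66, cross-overs removed); or d = 0.55 with 106 patients and no inflation (power 80.1%). The article states none of these effect sizes.

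**Step 5: is SNOT-22 itself covered?** Yes. 106/0.8 = 132.5, so 133 enrolled are enough and 150 exceeds that.

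**The case against.** The strongest reply is that the article nowhere says cross-over was left out of the ppFEV1 calculation. It says the SNOT-22 sizing was applied to Objective 1, which allows the reading that the same allowance was kept. The article is condensed, and the full protocol may hold the SD, the split and the handling of cross-over. All of this stands. A reader might infer from the silence that cross-over was omitted, and that true power on the plan's own inputs is 45% to 50%. The documents do not support that. Omission is only one reading, the 0.7 dilution is not stated, and 106 does not identify it. Nor does the article commit to analysis by initially elected group: it collects cross-over data throughout and lists propensity-score and instrumental-variable methods.

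A second reply is that the condition is disclosed: the sentence opens by assuming 170, and the text just before gives 170 as anticipated enrolment. That is fair, and the cost of this part alone is modest, about 5 percentage points. It remains that the power is quoted at a number above the study's own goal, and that no figure is given at the goal.

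Third, the word used is change, which could mean a change within a group. A between-group difference fits Objective 1 better, but this is a choice made here. Under a within-group reading the move from 170 to 150 still takes power from 80% to about 75%, since it depends only on the ratio of sample sizes; the cross-over rows of the table would not follow.

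Finally, the cohort is observational and sized on SNOT-22, for which 150 is adequate. The point therefore concerns how ppFEV1 power is reported, not whether the study is viable.

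**Conclusion.** The point holds in a limited form. The stated 80% power for 1.6 ppFEV1 points is not delivered at the recruitment goal: at 150 enrolled it is about 75%, with a detectable effect of about 1.7 points, and about 2.45 in place of 2.3 accounting for HEMT. This holds even on the most favourable reading, with cross-over already included. It rests on the article's own 1.6, 2.3, 170, 150 and 20%, and on an unchanged SD and split.

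The article also leaves open whether the 30% cross-over is in the ppFEV1 figures. If it is not, the readings examined put power at 150 between 18% and 61%. The 45% (50% at 170) and the 2.4-point detectable effect of surgery (2.3 at 170) are conditional on a 30% net dilution under analysis by initial group, and should not be read as the power of this design.

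**What to change.** In Statistical power and sample size, restate both ppFEV1 figures at the goal of 150 enrolled (120 evaluable) and on the same cross-over assumption as SNOT-22. Give the SD, the ESS:CMT split and the cross-over handling actually used, and say whether the figures are differences between groups.

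- If cross-over was already included, the restated detectable effects are about 1.7 points, and about 2.45 accounting for HEMT.
- If it was not, recompute with the direction and handling that the analysis will use. Quote 2.4 points only as the result conditional on a 30% net dilution.
- Figures at 170 may stay alongside, labelled as the anticipated enrolment.

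The cost is wording and a short recalculation by whoever holds the original inputs. The published detectable effect becomes less favourable. No extra patients are needed, and design and data collection do not change.

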**Fig 1 pone.0310986.g001:**
[figure not shown]
Unaccounted factors in endoscopic sinus surgery decision-making for people with cystic fibrosis. ESS, endoscopic sinus surgery; CMT, continued medical therapy; PwCF+CRS, people with cystic fibrosis and comorbid chronic rhinosinusitis; CF, cystic fibrosis, CRS, chronic rhinosinusitis; QOL, quality of life; ppFEV_1_, percent of predicted expiratory volume in the first second.

The CF treatment landscape is rapidly transforming with the introduction of CF transmembrane conductance regulator (CFTR) modulator therapies. The triple combination therapy elexacaftor/tezacaftor/ivacaftor (ETI) is clinically available in the United States (US) for ~90% of people with CF > 2 years of age based on variant status and considered a HEMT [8]. ETI therapy has been associated with improved sinus computed tomography (CT) scan scores and CRS symptom severity, but does not fully resolve the symptoms of CRS in adults even with extended therapy for up to two years [9, 10]. While ETI has demonstrated high treatment efficacy, approximately 10% of people in the US are not eligible based on variant status and still others may not be able to tolerate the medication due to potential side effects [11]. Understanding the impacts of ESS in the modern era, while accounting for the effect of ETI, remains critical for the CF community.

Prior research on pulmonary outcomes after ESS has produced mixed results [12, 13], and has mainly consisted of small, retrospective studies. The current research landscape on ESS in PwCF is largely limited to retrospective case-control studies, constrained by patient numbers and the challenges of randomizing surgical interventions. This prospective, multi-institutional cohort-study aims to comprehensively determine the impact of ESS on PwCF+CRS in the era of highly effective modulator therapy.

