### Statistical methods

For all objectives, we will verify predictive model assumptions and test goodness-of-fit, considering alternative models if needed. We will account for potential site-specific differences as fixed effects in our models. Other methods to address site clustering include mixed effects models and generalized estimating equations.

For Objective 1, mixed effects model will be used to assess the impact of ESS versus CMT on ppFEV_1_ changes at initial and subsequent visits. Fixed effects will include baseline FEV1 (FEV1 > 80% predicted, <80% and > 50%, and <50%), CF variant status, use of CFTR modulator therapy, sex, prior sinus surgery, time and treatment; patients will be treated as random effects. An unstructured variance approach will model within-subject errors, and we will explore other covariance if needed. As exploratory analysis, we will compare ppFEV_1_ from a year before enrollment to post-treatment values using the same model. Using a generalized linear model with a Poisson distribution and prior year data, we will assess the impact of ESS versus CMT on exacerbation rates and antibiotic use, complemented by descriptive statistics for sociodemographic factors.

For Objective 2, we will describe patient characteristics using summary statistics. Treatment effects on patient reported-outcome measures (CFQ-R, SNOT-22, PHQ-9, PSQI, CFQ, QOD, and SIT) will be explored via a mixed effects model, adjusting for multiple comparisons using a gate-keeping procedure and assessing for self-report bias in patient-reported outcomes by comparing them to FEV1.

For Objective 3, we will correlate productivity costs with patient demographics, disease factors, pulmonary status, and QOL impairment. We will use a mixed effects model to evaluate these outcomes.

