## Discussion

In this multi-institutional prospective study, our primary objective is to evaluate post-ESS outcomes in PwCF+CRS in the era of highly effective modulator therapy. We will examine pulmonary function, PEx rates, antibiotic use, QOL, productivity loss, and health utility value over a 12-month period post-ESS. Our study uniquely will compare the impact of HEMT on outcomes between PwCF+CRS who undergo ESS and those opting for CMT.

Our study leverages a prospective, multi-institutional design, mitigating the limitations of small sample size and common biases associated with retrospective review. We acknowledge the limitations of an observational design instead of a randomized controlled clinical trial (RCT). This design was selected based on challenges of randomizing surgical interventions and PwCF’s reservations about randomization to ESS or delayed intervention [35]. Many PwCF expressed reluctance to be randomized, which would likely have led to enrollment difficulties in a RCT [35]. Further, there are notable difficulties in randomizing study participants to surgical interventions that require general anesthesia. These include the high cost of interventions that the study may have to fund (ESS estimated at > $10,000 USD/case) [36] and ethical considerations, such as employment of sham surgery in a placebo control arm [37]. To minimize potential bias, we will employ advanced statistical techniques like MPA and propensity score matching. Our method is poised to produce robust data, including endpoints that can provide some of the first insights of CRS outcomes in the current era. Data accumulated from this study will provide preliminary data upon which to design future trials.

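### The promised comparison of HEMT impact between ESS and CMT has no matching term in the stated ppFEV1 model, and the 2.3-point detectable change cannot be the figure for it

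*Protocol article*

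**What the plan says.** **Aim.** The Discussion states: "Our study uniquely will compare the impact of HEMT on outcomes between PwCF+CRS who undergo ESS and those opting for CMT". It later speaks of exploring how post-surgical outcomes and HEMT interact. Objectives & endpoints is more modest: there, ESS is to be compared with CMT with HEMT taken into account.

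**Model.** For ppFEV1, Statistical methods specifies a mixed effects model. After categorised baseline FEV1, the fixed effects are "CF variant status, use of CFTR modulator therapy, sex, prior sinus surgery, time and treatment". No treatment-by-modulator term is named. The only subgroup analysis named in that section is in surgically naive participants.

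**Power.** Under Statistical power and sample size, "Type I error will be controlled at two-sided 5% level". On ppFEV1 the article says that "previous mixed results complicate clear expectations to use in power calculations for objective 1". The enrolment basis for its two detectable changes is worded as "Assuming 170 participants (factoring in 20% dropout". The first of them is put this way: "we will have 80% power to detect a 1.6% ppFEV_1_ change for objective 1". The second, 2.3 points at the same power, is described only as the "change for objective 1 accounting for HEMT". No SD, within-patient correlation, test, ESS:CMT ratio or HEMT share is given for either figure.

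**HEMT share.** The Introduction says that the triple combination is "clinically available in the United States (US) for ~90% of people with CF", above a minimum age. It does not say what share of this cohort takes it.

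**The concern.** Comparing the impact of HEMT between two treatment groups is a question of effect modification: is the ESS-minus-CMT difference in ppFEV1 the same on and off HEMT? A main effect for modulator use removes average differences between users and non-users. It assumes that the treatment effect is the same in both. The listed covariate is also any CFTR modulator, whereas the Introduction treats HEMT as a distinct class.

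The power statement adds to the difficulty. A reader who sets the Discussion beside the 2.3-point figure will conclude that the study has 80% power to find a 2.3-point difference in the ESS effect by HEMT status. A null result could then be read as evidence that ESS works equally well with and without HEMT, when the study had little chance of showing otherwise.

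**Working it through.** **Inputs from the article (Statistical power and sample size).** Two-sided 5% level; 80% power; detectable changes of 1.6 and 2.3 points; 170 participants with 20% dropout, so 170 × 0.8 = 136 evaluable.

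**Assumptions, because the article is silent.** The 1.6 figure is an ESS-versus-CMT contrast, the residual SD is common to all groups, and the HEMT share p lies between 50% and 90%.

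**1. Can the stated figures be reproduced?** Not in absolute terms, since no SD is given. Solving back with 1:1 groups, 1.6 = (1.960 + 0.842) × SD × √(4/136) gives an SD of change of about 3.3 points (about 3.7 if all 170 are evaluable). The ratio can be checked without the SD or N:

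- 2.3 / 1.6 = 1.44. With rounding it lies between 2.25/1.65 = 1.36 and 2.35/1.55 = 1.52.

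**2. What would give that ratio?**

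- *A comparison within a fraction p of the sample:* detectable change = 1.6/√p. At p = 0.5 this is 1.6 × 1.414 = 2.26, which rounds to 2.3. Allowing for rounding, the implied fraction runs from 1/1.52² = 44% to 1/1.36² = 54%.
- *Covariate adjustment in the whole sample:* the variance would have to rise by 1.44² = 2.07, an R² of 1 − 1/2.07 = 0.52 between treatment and the covariates. This is possible in a non-randomised cohort, but nothing in the article suggests it.

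**3. What is the detectable ESS-by-HEMT interaction?** Let an arm hold a patients on HEMT and b off. The variance of the difference between HEMT strata in that arm is SD²(1/a + 1/b), and 1/a + 1/b ≥ 4/(a + b). Summed over both arms, the interaction variance is at least four times that of the whole-sample ESS-versus-CMT difference, so its standard error is at least double:

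- floor = 2 × 1.6 = 3.2 points, for any allocation ratio and any HEMT share. Even at the lower rounding limit of 1.6, 2 × 1.55 = 3.1, which exceeds 2.35.

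With the same HEMT share p in both arms, the detectable interaction is 1.6/√(p(1 − p)):

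| Share on HEMT (assumed) | Detectable interaction | Power for 2.3 points | Evaluable N for 2.3 points at 80% power |
|---|---|---|---|
| 50% | 1.6/0.50 = 3.2 | 52% | 263 |
| 70% | 1.6/0.458 = 3.5 | 45% | 313 |
| 80% | 1.6/0.40 = 4.0 | 36% | 411 |
| 90% | 1.6/0.30 = 5.3 | 23% | 731 |

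The last column is 136 × (detectable interaction/2.3)², against 136 evaluable.

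**4. Recruitment target.** The 1.6 figure uses 170. At the stated goal of 150, detectable changes rise by √(170/150) = 1.065, so the interaction becomes 3.4, 4.3 and 5.7 points at 50%, 80% and 90%.

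**The case against.** **The objective asks only for adjustment.** Objectives & endpoints speaks of taking HEMT into account, and a fixed effect does that. This stands for that wording. It does not cover the Discussion, which promises a comparison, and it leaves unexplained why an adjusted analysis should have a detectable change 44% larger.

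**The list of fixed effects is condensed.** It also omits treatment by time, which a model of change would need, so an interaction may sit in a fuller plan. This is fair, and it limits the point to what the article states. But the article does name its terms and does attach a power figure to HEMT, and those two should match its own aim.

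**The article never calls 2.3 an interaction.** True. The finding is that the contrast is unlabelled and that the reading invited by the Discussion is arithmetically excluded. If 1.6 were instead a within-patient change, the two-group figure would exceed 1.6 and the interaction floor would exceed 3.2.

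**Stronger readings that a reader might infer, and that the article does not support:**

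- *The HEMT question cannot be answered.* Table 3 collects modulator data at every visit, and Baseline measures records modulator details and genotype. An interaction or stratified estimates can therefore be fitted; the limit is precision.
- *The 2.3 is a half-sample figure, or a miscalculation.* The match with √2 is suggestive, but without an SD, test or HEMT share it stays an inference.
- *About 90% of this cohort is on HEMT.* That figure is US eligibility for one product. The Introduction notes that some people cannot tolerate it, Table 1 excludes recent and anticipated modulator starters, and the study was designed in 2018, before that product's approval. The cohort's share may be well below 90%.

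**Conclusion.** The point holds as a mismatch between aim, model and power statement. The model as described adjusts for any CFTR modulator and does not estimate whether the effect of ESS on ppFEV1 differs by HEMT, although the Discussion presents that comparison as the study's distinctive contribution. The contrast behind 2.3 points is not stated. On the same scale as the stated 1.6, it cannot be the detectable ESS-by-HEMT interaction.

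The floor of 3.2 points needs a common residual SD and a shared contrast, but not 1:1 allocation or any particular HEMT share. The larger values (4.0 at 80%, 5.3 at 90%) also need equal HEMT shares in the two arms and rest on assumed shares. Even in the best case, power for a 2.3-point interaction is about one half. The correction should be made, but it does not undermine the main ESS-versus-CMT analysis.

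**What to change.** 1. State whether HEMT is treated as a confounder, an effect modifier or both, and align the Objectives and Discussion wording.
2. Code HEMT separately from other CFTR modulators.
3. Add a treatment-by-HEMT term, with time, to the ppFEV1 model, and name it as the analysis for the HEMT comparison.
4. State which contrast 2.3 refers to, with the SD, test, HEMT share and N behind both 1.6 and 2.3.
5. For the HEMT comparison, report the detectable interaction at the observed HEMT share. If it is too large to be useful, label the comparison exploratory and give estimates with confidence intervals.

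The cost is one extra model term with its time component, some rewording, and a less favourable stated figure. No new data are needed, and enrolment was still open at the article's status date.
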